### Hypotheses & research questions

All research questions explicitly addressed in the research project are listed in Table 1.

**Table 1 Tab1:** Dedicated hypotheses & research questions

Quantitative Hypotheses (A) Determinants of Patients PP Usage	
A1	The relative proportion of patients using DAC with low digital literacy increases over the observation period
A2	The relative proportion of patients using DAC with low health literacy increases over the observation period
A3	The relative proportion of patients using DAC with low technology acceptance increases over the observation period
A4	Patients planned for inpatient treatment are more likely to use DAC than patients receiving acute outpatient care
A5	Patients who are frequently treated in the hospital (either outpatient or inpatient) are more likely to use DAC than those who are less frequently treated
Quantitative Hypotheses (B) Determinants of Physicians PP Usage	
B1	The relative proportion of physicians using DAC with low digital literacy increases over the observation period
B2	The relative proportion of physicians using DAC with low technology acceptance increases over the observation period
Qualitative Research Question (C) Barriers to PP Usage or Reasons for Non-Usage	
C1	What are the patient-related reasons for non-usage and barriers during the usage of DAC over time?
C2	What are the physician-related reasons for non-usage and barriers during the usage of DAC over time?
Exploratory Research Question (D) Actual PP Usage	
D1	How does the documentation of medical history change over time with the utilization of DAC through the PP?
Exploratory Research Question (E) Changes in Administrative Data	
E1	What changes occur in the data collected for administrative purposes after the introduction of the PP?

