All physicians working in the three clinics at the three measurement time points (t0; t1; t2) receive digital questionnaires. These questionnaires include questions to measure physician-related determinants and additionally, in t1 and t2, questions regarding usage behavior. The surveys of physicians are based on already existing and validated scales (e.g. digital literacy [26], technology acceptance [20], or, if not possible, on items developed according to methodological standards [23]. Additionally, socioeconomic and sociodemographic factors (e.g., age, gender, work experience) are recorded for later adjustment. Due to the legal situation, physicians must inevitably use the PP in their everyday work. Nevertheless, they can use the PP, in this case the DAC, differently depending on which type of innovation adopter they belong to according to the DOI. For example, the *late majority* may only use the absolute basics, mandatory functionalities of the PP while the *innovators* also use additional advanced features, which may be optional to use. Therefore, in this project, the perceived benefit of the DAC is examined as the dependent variable, instead of the binary actual use, as it is done for the patients. Due to the organizational pressure to use, a stronger effect on physician PP usage can be expected. Based on an assumed effect size of Cohen’s D = 0.35, a power of 80%, and a significance level of 0.05 in a two-sided paired t-test, the required sample size is *N* = 66 physicians per time point, cumulated across the three clinics. A comparison of physicians between clinics at each time point will not be conducted due to the otherwise higher required sample size. The invitation to participate and access to the digital questionnaire will be distributed through internal channels, emphasizing the practical relevance of the survey for the medical staff and positively influencing the willingness to participate. The data analysis will be conducted using descriptive and inferential statistics, adjusting for socioeconomic and sociodemographic characteristics, and performed with the statistical software SPSS^©^.

C)Analysis of barriers to PP usage and reasons for non-usage

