Interviews will be conducted with patients who are treated on an outpatient or inpatient basis at the three clinics during the measurement time points t1 and t2 and used or did not use the digital anamnesis. In addition, interviews will be conducted with physicians who are working on an outpatient or inpatient basis at the three clinics during the measurement points t1 and t2 and used or did not use the digital anamnesis. Based on Rogers' DOI [25], the reasons for non-usage and experienced barriers during the use of the DAC can change with the PPs increasing existence. Therefore, interviews will be conducted at both t1 and t2. The semi-structured interviews will include questions regarding the subjectively perceived barriers during the usage or reasons for non-usage.

In each of the three clinics, a total *n* = 12 interviews with patients will be conducted at each measurement time point (t1 & t2). Purposeful sampling will be employed, varying different patient characteristics (e.g., age, education) to achieve theoretical saturation [22]. The total of *N* = 72 interviews will be conducted either in person, for example, during treatment at the clinic's premises, or by telephone according to the participants' preference. Moreover, *n* = 4 interviews with physicians will be conducted in each of the three clinics at each measurement time point (t1 & t2). Purposeful sampling will be employed, varying different physician characteristics (e.g., age, specialty, ambulatory/inpatient setting) to achieve theoretical saturation [22]. The total of *N* = 24 interviews will take place in the clinics and, if possible, during working hours. This reduces the effort for the interviewees and increases the willingness to participate. Depending on the participants' preference, the interviews can also be conducted by phone. All interviews, estimated to last 45 min, will be recorded, transcribed, and anonymized. Subsequently, the data will be analyzed using content analysis [19] with the assistance of the MAXQDA^©^ 2024 software. 

D)Analysis of actual PP usage

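### B1 and B2 concern the make-up of physicians who use the DAC, but the stated dependent variable is perceived benefit, so the stated analysis does not test them

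*Protocol article*

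**What the plan says.** **Hypotheses (Table 1).** B1 reads "The relative proportion of physicians using DAC with low digital literacy increases over the observation period". B2 reads "The relative proportion of physicians using DAC with low technology acceptance increases over the observation period". Both describe the composition of a group of users.

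**Outcome (Methods / design, part B).** The article states "Due to the legal situation, physicians must inevitably use the PP in their everyday work", but adds that "they can use the PP, in this case the DAC, differently depending on which type of innovation adopter they belong to": some may keep to the compulsory basics while others also use optional features. It concludes that "in this project, the perceived benefit of the DAC is examined as the dependent variable, instead of the binary actual use", binary use being kept for the patients. The physician questionnaires measure determinants at all three waves and "additionally, in t1 and t2, questions regarding usage behavior".

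**Sample size (same part).** N = 66 physicians per time point across the three clinics, from a two-sided paired t-test with d = 0.35, 80% power and significance level 0.05.

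**Interviews (Methods / design, part C).** The article says that "interviews will be conducted with physicians who are working on an outpatient or inpatient basis at the three clinics" at t1 and t2, and the sentence goes on to cover both those who used the digital anamnesis and those who did not. C2 in Table 1 asks for physicians' reasons for non-usage.

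**The concern.** To examine B1 or B2 as worded, each physician must be classed as a DAC user or not, and the low-literacy or low-acceptance share among users must be compared across waves. Part B sets binary use aside and analyses a different quantity, one that no hypothesis in Table 1 mentions.

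The main risk is in reporting. A finding on perceived benefit could be presented as confirming or refuting a hypothesis about use. A second risk arises only if the user share is computed after all: where nearly every physician is a user, that share moves with staffing, response or literacy itself, and such a movement could be read as diffusion. Part C adds an inconsistency, because it expects physician non-users while part B drops binary use on the ground that use is compulsory.

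**Working it through.** **1. The plan's own figure.** Inputs from part B: d = 0.35, two-sided 0.05, power 80%, paired t-test.
- Normal approximation: ((1.960 + 0.842)/0.35)² = 64.07, i.e. 65.
- Noncentral t: n = 66.02.

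The stated 66 reproduces. It is the size for a change in a continuous mean between linked measurements. That fits a perceived-benefit score. It fits neither a proportion among users nor the association of literacy with benefit: mean benefit can rise from t1 to t2 while that association stays the same.

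**2. What B1 measures.** By Bayes' rule, with L = low literacy and U = user,

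P(L | U) = P(U | L) × P(L) / P(U).

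If every physician uses the DAC, P(U | L) = P(U) = 1 and P(L | U) = P(L) at every wave. The B1 contrast then carries no information on adoption at any sample size. If some physicians bypass the DAC, P(U | L) can change over time and the contrast does carry such information. The same holds for B2.

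**3. N = 66 applied to a proportion (illustration).** The article gives no base share, so the shares below are assumptions. Two independent groups of 66, two-sided 0.05, pooled-variance normal formula:

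n per wave = (1.960·√[2p̄(1−p̄)] + 0.842·√[p₁(1−p₁)+p₂(1−p₂)])² / (p₂−p₁)².

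| Assumed share at t1 | Share at t2 needed for 80% power | Power for a 10-point rise | n per wave for a 10-point rise |
|---|---|---|---|
| 10% | 29% | 36% | 199 |
| 20% | 42% | 26% | 294 |
| 30% | 54% | 22% | 356 |
| 40% | 64% | 21% | 388 |

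**4. N = 66 applied to a change in association (illustration).** Assume independent waves of 66 and compare the correlation of literacy with perceived benefit at t1 and t2 on the Fisher z scale.
- SE = √(1/63 + 1/63) = √(2/63) = 0.178.
- Difference needed for 80% power: (1.960 + 0.842) × 0.178 = 0.50.
- From r = 0.50: atanh(0.50) = 0.549; 0.549 − 0.50 = 0.05; tanh(0.05) = 0.05.

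The correlation would have to fall from 0.50 to about 0.05.

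**5. The passages side by side.**

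| Place | Quantity or premise |
|---|---|
| Table 1, B1 and B2 | Low-literacy or low-acceptance share among DAC users |
| Part B, outcome | Perceived benefit; binary use set aside |
| Part B, sample size | Paired difference in a mean |
| Part C and C2 | Physicians who did not use the DAC exist |

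The first three rows name three different targets. The fourth conflicts with the reason given for the second, unless compulsory portal use leaves room to bypass the DAC.

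**The case against.** The strongest reply is that part B recognises the problem and answers it openly: use is compulsory, the manner of use varies, so perceived benefit is analysed. On this view only the wording of Table 1 lags behind, and the link from hypothesis to model belongs in a full protocol or analysis plan. The first half is fair. The second does not remove the point, because the article itself fixes both the hypotheses and the dependent variable, and they disagree.

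A reader might infer that B1 and B2 can never be tested, or that DAC use is 100% and the hypotheses are empty. The article does not support either reading:
- Compulsory use is stated for the portal. Background (Relevance) presents the DAC as one tool of the portal, and part B allows it to be used to differing degrees.
- Usage behaviour is asked at t1 and t2, so a user group or a graded measure might be built from those items.
- Part C expects physicians who did not use the DAC.

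It is also tempting to say that extent of use should replace perceived benefit as the main outcome. The content of the usage items is not shown, so that cannot be assumed to be feasible. Nor can it be said that perceived benefit fails to reflect adopter type, since its items are not shown either. Finally, the risk of staff mix passing for diffusion is limited: part B does not make the user share its outcome, and adjustment for characteristics such as age, gender and work experience is planned.

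**Conclusion.** The point stands in a bounded form. B1 and B2, both of the physician hypotheses, cannot be tested with the stated dependent variable, and the sample size was derived for yet another quantity. This is a contradiction within the article, not detail left out of it. The arithmetic behind N = 66 is correct for what it calculates.

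The statement that the user share carries no information on adoption is conditional: it holds to the extent that DAC use is universal, which the article neither states nor rules out. The power figures for proportions and correlations rest on independent waves of 66 and on assumed base values. They show that 66 does not carry over to those tests and do not predict the study's results.

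**What to change.** Before the physician data are analysed, reconcile Table 1 with Methods, parts B and C:

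1. **Restate B1 and B2 in terms of the stated outcome**, for example: the association of digital literacy (B1) or technology acceptance (B2) with perceived benefit of the DAC weakens from t1 to t2. Test each with a determinant-by-wave interaction. This matches the Abstract, which asks whether the strength of the factors changes over time and names regression models.
2. **Keep benefit and use apart in reporting.** If the planned usage items distinguish basic from optional functions, report extent of use alongside. Do not call perceived benefit use.
3. **State what N = 66 covers:** 80% power for a paired mean difference of d = 0.35, and not the interaction. Give the detectable change in association, roughly 0.50 to 0.05 for independent waves of 66.
4. **Keep physician non-usage in C2**, since it could reveal bypassing of the DAC, but state whether physicians can bypass it, so that parts B and C agree.

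The cost is two reworded hypotheses, an update of the registry entry and a less favourable power statement. No extra participants are needed, and step 1 needs no new survey items.

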## Methods / design

The study follows a longitudinal triple cross-sectional design (pre-post-post). It is based on three consecutive data collection phases, conducted in three clinics of a large academic teaching hospital in Germany. Data will be collected in each of the three clinics 2 months before the implementation (t0), as well as 6 months (t1) and 12 months (t2) after the implementation of the PP. Each of the three clinics has an eight-week period allocated for data collection to achieve the targeted case numbers described below. Quantitative data from surveys of patients (A) and physicians (B), qualitative data from interviews with patients and physicians (C), as well as medical history documentation (D) and administrative data from a participating clinic (E) are used to answer the research questions (Fig. 2). Each of the research questions (A) – (E) will be presented in detail in the following, including detailed case number calculations or sampling strategies.

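### The 66 physicians per time point are 66 complete matched pairs, but the article counts them as respondents per wave in a cross-sectional design with no stated linkage, so the 80% power is conditional

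*Protocol article*

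**What the plan says.** The Methods / design section opens with the design: "The study follows a longitudinal triple cross-sectional design (pre-post-post". Waves fall 2 months before and 6 and 12 months after the portal goes live, so t0 to t2 spans 2 + 12 = 14 months.

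Part B defines who is surveyed: "All physicians working in the three clinics at the three measurement time points (t0; t1; t2) receive digital questionnaires". The sample size rests on Cohen's d = 0.35, 80% power and "a significance level of 0.05 in a two-sided paired t-test, the required sample size is" then given as "66 physicians per time point, cumulated across the three clinics". The larger effect than in the patient survey is explained in one sentence: "Due to the organizational pressure to use, a stronger effect on physician PP usage can be expected".

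Part B describes no fixed physician cohort, person code or matching of questionnaires, and makes no allowance for physicians who answer in one wave but not another. It does not say whether 0.35 is standardised by the SD of paired differences or by the SD between physicians.

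**The concern.** A paired t-test works on within-person differences, so its sample size is the number of people measured twice and matched. A target of respondents per wave is a different quantity. Sixty-six answers at one wave and 66 at the next give 66 pairs only if the same 66 people answered both times and can be identified as such.

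Hypotheses B1 and B2 rest on this sample. Without a link the test used for sizing cannot be run, and the power of an unpaired comparison depends on quantities the article does not give. With a link, every physician who answers only one of the two waves reduces the number of pairs. A link also cannot easily be added afterwards: if the t0 questionnaires carry no code, pairs involving t0 are lost.

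**Working it through.** **Inputs from part B:** d = 0.35, two-sided alpha 0.05, power 80%, paired t-test, 66 per time point.

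**Assumed, because the article does not give them:** the within-person correlation rho between waves, equal SD in both waves, and the share of 66 respondents who can be matched.

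**1. The article's own figure.** Power of a two-sided paired t-test comes from the noncentral t distribution with df = n − 1 and noncentrality d·√n.
- n = 66: 0.35 × √66 = 2.84, power 79.99%.
- n = 67: power 80.6%.
- Normal approximation: ((1.960 + 0.842)/0.35)² ≈ 64.1.

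The stated 66 is reproduced within rounding, with n counting complete pairs and 0.35 standardised by the SD of the paired differences (dz).

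**2. Waves analysed as independent, 0.35 on the between-person SD.** Two-sample t-test with df = 2n − 2 and noncentrality d·√(n/2).
- n = 66 per wave: 0.35 × √33 = 2.01, power 51.4%.
- 80% power needs 130 per wave.

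**3. Waves analysed as independent, 0.35 is dz.** The between-person effect is then d = 0.35 × √(2(1 − rho)).

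| Assumed rho | Between-person d | Power, 66 per wave | n per wave for 80% |
|---|---|---|---|
| 0 | 0.495 | 81% | 66 |
| 0.3 | 0.414 | 66% | 93 |
| 0.5 | 0.350 | 51% | 130 |
| 0.7 | 0.271 | 34% | 215 |

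Steps 2 and 3 agree only at rho = 0.5, where √(2(1 − 0.5)) = 1.

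**4. Waves linked, but not every respondent matched.** Paired test on the matched pairs only, dz = 0.35, exactly 66 respondents per wave.
- 80% matched: 0.8 × 66 ≈ 53 pairs, power 71%.
- 60% matched: 0.6 × 66 ≈ 40 pairs, power 58%.

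Read the other way, 66 pairs need 66/0.8 = 82.5, so 83 respondents per wave, or 66/0.6 = 110.

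**The case against.** The article does not say that the physician questionnaires are unlinked, and it says nothing about staff turnover. It also calls the design longitudinal, and it invites the whole physician staff of the same three clinics each time, so overlap is likely and matching is feasible. A coding procedure is the kind of detail a condensed article may leave to the full protocol. All of this stands: a reader might infer that the waves are unlinked and that power falls to 51%, but the documents do not establish either. On the other hand, the word paired is weak evidence of a planned link, because part A uses the same test for the patient waves. And a coding procedure elsewhere would not turn a count of pairs into a count of respondents.

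The 66 is a requirement and not a cap. Staff numbers are not given, and more respondents could deliver 66 pairs. The 71% and 58% therefore hold only for exactly 66 respondents at the assumed match rates.

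A reader might also infer that 0.35 is too large because compulsory use leaves less variation between physicians. That does not follow. The sized test concerns a mean change, and for a given change a smaller SD raises Cohen's d. The article labels 0.35 an assumption and explains how use can still differ between physicians. Power at the patients' effect size of 0.2 shows no error either, since the article does not assume that value for physicians.

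**Conclusion.** The point holds in conditional form. The 66 is correct as a number of complete pairs but is stated as respondents per wave, in a design described as cross-sectional with no linkage stated. The 80% is therefore assured only if 66 physicians answer in both compared waves and are matched.

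No single figure replaces it:
- **Unlinked:** about 51% if 0.35 is on the between-person SD. If 0.35 is dz, 81% down to 34% for correlations from 0 to 0.7. The 80% survives without linkage only near zero correlation, which is unlikely when the same physicians answer the same scales twice.
- **Linked:** 71% or 58% with 53 or 40 pairs.

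The correlations and match rates are assumptions of this review. The statement that power is 51%, without those conditions, is not supported.

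**What to change.** - Restate 66 as the number of complete pairs needed for the comparison, and say whether 0.35 refers to the SD of paired differences or the between-person SD.
- Put a self-generated pseudonymous code on the physician questionnaires at t0, t1 and t2. If a linkage procedure already exists in the full protocol, state it here.
- Analyse all answers with a model that uses matched and unmatched responses: a random effect for physician, fixed effects for clinic and wave.
- Replace the unconditional 80% with the power for the number of pairs expected, and give the unlinked case with its assumptions.

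The cost is one code item, a data-protection sentence and a slight risk of lower response. Reaching 66 pairs may require more than 66 respondents per wave. If the clinics cannot supply them, the stated power has to be lowered.

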**Fig. 2 Fig2:**
[figure not shown]
MAiBest study design

A)Analysis of determinants of patients PP usage

The trend survey at the three measurement time points (t0; t1; t2) allows for the depiction of determinants of PP usage and the expected changes in these determinants over time. The t0 survey captures the clinic-specific heterogeneity of patient-related determinants for PP use and enabling an adjustment of the trend analysis for these baseline values from t0. This facilitates the examination of trends within each clinic and allows for comparisons between the three clinics. Patients treated in the three clinics at the three measurement time points (t0; t1; t2), whether inpatient or outpatient, will receive a paper-based questionnaire with additional, optional access to a digital version. These questionnaires include items measuring patient-related determinants and, additionally, usage behavior in t1 and t2. The patient surveys are based on existing and validated scales (e.g. digital literacy [26], technology acceptance [20], or if not possible, on items developed according to methodological standards [23]. Additionally, socioeconomic and sociodemographic factors (e.g., age, gender, education, income) are recorded for later adjustment.

The sample size calculation results in a required rounded *N* = 200 patients per measurement time point per clinic (pooled total *N* = 1800). This is based on an assumed weak effect size for Cohen's D of 0.2 with 80% power and a significance level of 0.05 for a (1) two-sided independent two-sample t-test for the comparison between clinics at each measurement time point (total *N* = 393 at each time point for the comparison between two clinics, rounded *n* = 200 per clinic) and (2) for the comparison within the clinic across measurement time points in a two-sided paired t-test (required *n* = 198 per time point). The data analysis is performed using descriptive and inferential statistics, adjusting for previously collected socioeconomic and sociodemographic characteristics, conducted with the statistical software SPSS^©^.

B)Analysis of determinants of physicians PP usage

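### The physician analysis pools three clinics without clinic in its stated adjustment, so a shift in which clinics respond may appear as, or hide, a time trend

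*Protocol article*

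**What the plan says.** The opening of Methods / design states: "The study follows a longitudinal triple cross-sectional design (pre-post-post"). Part B then describes the physician survey. "All physicians working in the three clinics at the three measurement time points (t0; t1; t2) receive digital questionnaires", and the target is 66 "physicians per time point, cumulated across the three clinics", from a two-sided paired t-test with d = 0.35, 80% power and a significance level of 0.05. No number per clinic is set. The article adds: "A comparison of physicians between clinics at each time point will not be conducted due to the otherwise higher required sample size".

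On adjustment, part B says that "socioeconomic and sociodemographic factors (e.g., age, gender, work experience) are recorded for later adjustment" and closes by describing the analysis as "adjusting for socioeconomic and sociodemographic characteristics, and performed with the statistical software" SPSS. Clinic is not named as a covariate, stratum or random effect.

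Part A treats clinic differently for patients. It sets 200 patients per clinic per time point, plans comparisons within each clinic over time, and says that the t0 survey "captures the clinic-specific heterogeneity" of patient-related determinants.

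**The concern.** B1 and B2 in Table 1 are statements about change over the observation period among physicians. When separate cross-sections are pooled over clinics, the contrast between two waves has two parts: change within clinics, and change in the share of respondents that each clinic contributes. Age, gender and work experience do not stand in for clinic, so the stated adjustment does not separate the two.

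In the patient part, the fixed number per clinic and the within-clinic comparisons hold the mix constant by design. Nothing stated for physicians does the same. At stake is whether an observed trend, or its absence, can be read as diffusion of the portal rather than as a change in who answered.

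**Working it through.** **1. The plan's own figure.** Inputs from part B: d = 0.35, power 80%, two-sided 0.05, paired t-test.

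- Normal approximation: n = ((1.960 + 0.842)/0.35)² = 64.07, so 65.
- With the usual small-sample term: 64.07 + 1.960²/2 = 65.99, so 66.
- Exact noncentral t: 67, with power 0.7999 at n = 66.

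The stated 66 reproduces. The arithmetic of the sample size is not the problem here.

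**2. Composition shift in a pooled mean.** With no change inside any clinic, the expected difference between waves is the sum over clinics of (change in share × clinic mean). The documents give no clinic means, staff numbers or response shares, so everything below is assumed. Let one clinic differ by d_c SD from the common mean of the other two, and let its share of respondents go from 1/3 to 1/2. The shift is (1/2 − 1/3) × d_c = d_c/6.

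| Assumed clinic difference | Shift in pooled mean | Share of 0.35 |
|---|---|---|
| 0.3 SD | 0.3/6 = 0.050 SD | 14% |
| 0.5 SD | 0.5/6 = 0.083 SD | 24% |
| 0.8 SD | 0.8/6 = 0.133 SD | 38% |

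**3. Simulation of the time test.** Two waves of 66 independent physicians, no true change, 6,000 replicates. Clinic means are equally spaced, with the highest and lowest 0.2 to 1.0 SD apart.

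| Respondents per clinic, first to second wave | Expected spurious difference | Type I error without clinic |
|---|---|---|
| 22/22/22 to 16/22/28 | 0.02 to 0.09 SD | 5.3% to 6.2% |
| 22/22/22 to 11/22/33 | 0.03 to 0.17 SD | 5.6% to 13.3% |
| 30/21/15 to 15/21/30 | 0.05 to 0.23 SD | 6.0% to 21.7% |

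With clinic as a fixed factor, type I error is about 5% and bias about zero in every scenario. The artefact is negligible when clinics differ little or the mix moves modestly. It is substantial only when both are large.

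**4. Cost in degrees of freedom.** For two waves, residual degrees of freedom go from 132 − 2 = 130 to 132 − 4 = 128.

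**The case against.** The strongest objection is that the quoted clause is a one-line summary in a condensed article. It does not say that nothing else is adjusted for, the variable list is given by example, and a fuller plan may include clinic. Part A closes with a nearly identical sentence, also without clinic, yet plainly handles clinic elsewhere. This is fair as a caution: the article does not say that clinic is excluded. But part A handles clinic through its number per clinic and its within-clinic comparisons, and part B has neither. What part B does state (pooling, no number per clinic, adjustment for personal characteristics) is weaker than the same plan with clinic added.

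The second objection is that the sample size assumes a paired t-test. If the same physicians are linked across waves and stay in their clinic, a stable clinic effect cancels within person and the problem largely disappears. This stands, and the point is conditional on it. The article describes cross-sectional waves and no linkage, so the paired reading cannot be relied on as it is written.

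Third, the illustrations concern a pooled mean, whereas B1 and B2 concern the share of physicians with low literacy or low acceptance among users. A pooled share is exposed to clinic mix by the same mechanism, but the size of any bias in those exact quantities has not been derived.

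A reader might also infer more than the text supports:

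- That clinic was left out of the model for lack of sample size. The article gives sample size only as the reason for not comparing clinics at each time point.
- That response by clinic will differ between waves. All physicians are invited each time and no response figures are given, so unequal response is possible but not shown.
- That the article expects clinics to differ in their physicians. The heterogeneity that it mentions concerns patients.

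**Conclusion.** The point holds as a cheap improvement. As described, the physician analysis pools three clinics, sets no number per clinic, and names an adjustment that does not include clinic. With unlinked cross-sectional waves, a change in clinic mix may create or mask a time trend in B1 and B2.

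The size cannot be fixed from the documents. Under the assumed move from 1/3 to 1/2 and clinic differences of 0.3 to 0.8 SD, a pooled mean shifts by 14% to 38% of the planned effect. Milder assumptions make it trivial: the lowest simulated case is 0.02 SD, with type I error close to nominal. The 21.7% type I error is the top of an assumed range and not a forecast. The conclusion rests on waves that are not linked by physician, on clinics that differ in the measured variable, and on response shares that change. The article establishes none of the last two, and describes the first only through its cross-sectional design.

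**What to change.** Record clinic in the physician questionnaire at every wave, because the article does not say that it is captured and it may not be recoverable later. Add clinic as a fixed factor (two terms) to the pooled physician models for every comparison between waves. Report the number of respondents by clinic and wave. State in the same place whether physicians are linked across waves, since that decides how much the clinic term matters.

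The decision not to compare clinics can stay: the clinic terms are for adjustment and need not be tested or interpreted. The cost is one questionnaire item, one sentence and two degrees of freedom with about 66 physicians per time point. No extra participants are needed. The change removes the effect of a shift in mix between clinics; it does not address selective response within a clinic.
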